**Figure 2 F2:**
[figure not shown]
**Calculation of volumes of uterus, uterine fibroids and bilateral ovaries by use of transvaginal ultrasonography**.

#### Improvement of subjective symptoms

11-point symptom score are evaluated in all patients 12 months after surgery. Symptoms by uterine fibroids are divided as follows; vaginal bleeding: pelvic pain: urologic symptom; gastrointestinal symptom; other symptoms (Fig. 3). After the completion of the current study, the results are compared between LUAL and LAVH.

**Figure 3 F3:**
[figure not shown]
**11-point symptoms score for evaluating of postoperative symptoms 12 months after surgery**.

#### Evaluation of postoperative vaginal bleeding

We have made "Bleeding Chart Score" by use of a simple visual assessment technique (Fig. 4) [10]. After we educate patients treated with LUAL, in particular, patients with preoperative symptoms such as menorrhagia and intermittent vaginal bleeding, about a simple visual assessment technique, they should record the amount of vaginal bleeding using the technique by her monthly. Thereafter, we calculate and record the amount of vaginal bleeding in the Bleeding Chart Score. After the completion of the current study, we will analyze the change of the amount of vaginal bleeding between preoperatively and 12 months after surgery.

**Figure 4 F4:**
[figure not shown]
**Bleeding chart score by a simple visual assessment technique for evaluating vaginal bleeding in patients treated with laparoscopic uterine artery ligation**.

#### Postoperative clinical outcomes

1) Anemia, hormonal status and serum CA-125 levels

Serum hemoglobin levels are evaluated in acute and chronic phases. In the acute phase, we check serum hemoglobin levels preoperatively and 2 days after surgery for comparing the effect of intraoperative blood loss between LUAL and LAVH. In the chronic phase, we check serum hemoglobin levels every 6 months, and we will compare serum hemoglobin levels between the 2 treatment methods.

The evaluation of hormone status is important because Liu et al [5] have reported that 3.5% of patients presented with elevated FSH, suggesting that LUAL can affect preoperative hormonal status. Moreover, serum CA-125 levels are increased in uterine fibroids, whereas they are decreased after the treatment of uterine fibroids. It means that serum CA-125 levels may be one of indirect markers reflecting the change of uterine fibroids [14]. Thus, serum LH, FSH, E2 and CA-125 levels are checked preoperatively and every 6 months, and we will compare these values between the 2 treatment methods.

2) Operation time, hospitalization and recovery time to routine life

The operation time is recorded in all patients for the investigation of whether there is a significant difference in the time between LAUL and LAVH. All patients are discharged as soon as possible if they are considered not to be hospitalized, and we will evaluate hospitalization and recovery time to routine life in all patients because the 2 parameters may reflect the time from surgery to healthy status.

3) Postoperative pain

Pain intensity is measured with a visual analogue scale (VAS), a 100-mm horizontal line with anchors of no pain and worst possible pain. The VAS is scored by measuring in millimeters the distance from the side marked no pain to the edge of the mark made by the patient. Possible scores ranges from a minimum of 0 to a maximum of 100 mm. The VAS scale is presented to the patients individually by instructed nurses who are unaware of assignments. After the VAS scales are evaluated during postoperative 3 days, the sums of scores will be compared between LUAL and LAVH.

4) Conversion to laparotomy

Although the 2 surgical treatments are similar in terms of laparoscopic managements, LUAL can preserve uterus with exploration of retroperitoneal space and ligation of uterine artery. On the other hand, LAVH removes uterus without the exploration of retroperitoneal space. Thus, these differences can contribute the rate of conversion from laparoscopic approach to laparotomy. We will compare the rate of conversion to laparotomy between LUAL and LAVH.

6) Satisfaction of postoperative sexual intercourse

Since patients treated with LUAL have cervices while those treated with LAVH have no cervices postoperatively, types of surgical treatment can affect postoperative sexual intercourse. Thus, the change of satisfaction of sexual intercourse will be evaluated after 12 months after surgery. The satisfaction of sexual intercourse is scored on 3-point scales, consisting of -1 ('not satisfied'), 0 ('no change') and +1 ('satisfied').

7) Complications associated with surgery

We divided complications associated with surgery as follows: intraoperative complication; complication during hospitalization; complication within 1 month; complication within 12 months. Moreover, the severity of the complications is defined as follows [9].

(1) Grade 1: no consequence for the patients and necessitated no or only nominal treatment (e.g. arterial spasm, postpuncture hematoma, surgical wound hematoma, vaginal discharge, urinary retension, thigh paresthesia).

(2) Grade 2: necessitated non-life-threatening additional treatment and had no sequelae of patients (e.g. urinary infection, severe pelvic pain, renoureteral colic, vulvovaginitis, anal fissure).

(3) Grade 3: death or complication that represents a threat to the patient's life or a source of permanent sequelae (e.g. death, deep vein thrombosis, transfusion, intraabdominal abscess, vesical fissure, surgical wound abscess).

After the completion of the current study, we will compare these results between the 2 treatment methods.

### Statistical analysis

We will analyze all patients assigned randomly. After informed consent is obtained, blocked randomization is performed by the Medical Research Collaborating Center (MRCC), a central office, in Seoul National University Hospital. The number of participants to be assigned to each of the comparison groups is balanced within blocks. The central office is remote from patient recruitment centers. Thus, participants' details are provided by phone, and the allocation sequence is concealed to individual staffing in the central office until a participant is irreversibly registered.

An intention-to-treat analysis will be performed as the least biased way to estimate intervention effects in the current study. For the primary endpoint, patients with missing EORTC-QLQ-C30 outcomes will be excluded from analysis because they cannot be considered to show specified minimum outcomes of the intended intervention. Analysis of covariance (ANCOVA) will be applied to compare the QOL scores on the basis of EORTC QLQ-C30 between the 2 treatment methods, adjusting for baseline values. After we consider the overall baseline EORTC score, a level of p < 0.05 will be assumed that it indicates imbalance. Thereafter, we will declare the variable to be imbalanced, and then include baseline values of EORTC QLQ-C30 in the ANCOVA to adjust the final results.

Other comparisons between the 2 groups will be made with the use of a two-sided Student's t-test and the Mann-Whitney *U *test for continuous data and the chi-square test for categorical data. The original power calculation requires the enrolled of a total 200 patients to give a power of 90% to detect a difference of 10% in the EORTC QLQ-C30 score at 12 moths (the primary outcome) at the 0.05 significance level.

All independent data such as serious adverse events and recruitment rates will be reviewed by MRCC and the Institutional Review Boards (IRBs) in Seoul National University Hospital, Seoul National University Borame Hospital and Seoul National University Bundang Hospital every 6 months. Moreover, the informal interim analysis for preliminary results will be undertaken, which will inform us whether the current study will be continued or not and maintain the quality of data through balancing baseline data.

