### Primary outcome

Postoperative QOL 12 months after surgical treatment are evaluated using the European Organization for Research and Treatment of Cancer Quality of Life Questionnaire for Cancer patients (EORTC QLQ-C30) version 3.0., which has been validated to the simplified Korean version [8]. After the evaluation of postoperative QOL, the results will be compared between LUAL and LAVH.

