## Outcome measurements

### Primary outcome

After patients are enrolled and randomized, we interview them using EORTC QLQ-C30 before surgical intervention for the evaluation of preoperative QOL. Since the validity of the EORTC QLQ-C30 has already been demonstrated in Republic of Korea [8], and the authors responsible for the validation recommended its usefulness in the current study, we decided to apply it for the evaluation of postoperative QOL in patients with symptomatic uterine fibroids.

The EORTC QLQ-C30 is a 30-item core-cancer-specific questionnaire-integrating system for assessing the health-related QOL in patients participating in international clinical trials [11]. The questionnaire incorporates five functional scales (physical, role, cognitive, emotional, and social), three symptom scales (fatigue, pain, and nausea and vomiting), a global health and QOL scale, and single items for the assessment of additional symptoms commonly reported by cancer patients (e.g., dyspnea, appetite loss, sleep disturbance, constipation, and diarrhea), as well as the perceived financial impact of the disease and treatment [12]. All items are scored on 4-point Likert scales, ranging from 1 ('not at all') to 4 ('very much'), with the exception of two items in the global health/QOL scale which use modified 7-point linear analog scales [11]. After 12 months, all enrolled patients will be interviewed, and the results of EORTC QLQ-C30 will be compared with preoperative results of it (Fig. 1).

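### The primary analysis is described as intention-to-treat on all randomised patients, but its own exclusion rule makes it a complete-case analysis, for a reason that does not justify the exclusion

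*Protocol article*

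**What the plan says.** All the relevant text is in the Statistical analysis section of the protocol article, apart from the definition and timing of the endpoint.

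- Analysis set: "We will analyze all patients assigned randomly".
- Principle: "An intention-to-treat analysis will be performed as the least biased way to estimate intervention effects in the current study".
- Exclusion rule, in the sentence that follows: "patients with missing EORTC-QLQ-C30 outcomes will be excluded from analysis because they cannot be considered to show specified minimum outcomes of the intended intervention". It applies to the primary endpoint.
- Model: "Analysis of covariance (ANCOVA) will be applied to compare the QOL scores on the basis of EORTC QLQ-C30 between the 2 treatment methods". The baseline score is named as the covariate, but the section then appears to make its inclusion depend on a significance test for imbalance.
- Endpoint (Primary outcome, under Methods and design): "Postoperative QOL 12 months after surgical treatment are evaluated using the European Organization for Research and Treatment of Cancer Quality of Life Questionnaire".
- Timing (Primary outcome, under Outcome measurements): "After 12 months, all enrolled patients will be interviewed, and the results of EORTC QLQ-C30 will be compared with preoperative results of it". No QLQ-C30 between surgery and 12 months is described.
- Size: the power statement "requires the enrolled of a total 200 patients to give a power of 90" per cent carries no SD and no allowance for loss to follow-up.

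The article sets no imputation, missing-data assumption or sensitivity analysis beside the exclusion rule.

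**The concern.** Consecutive sentences commit the trial to two different analysis sets. An analysis of everyone randomised and an analysis of those with a 12-month questionnaire are the same only if nobody is missing. This is not a detail left to a fuller document, because the article itself fixes both the label and the rule.

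The reason given adds to the problem. If it means that women without a questionnaire are presumed not to have benefited, missingness is tied to outcome, and removing them is then what distorts the comparison. If it means only that they lack the minimum outcome data, it restates that they are missing and gives no ground for believing that the remaining women represent them.

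The design leaves little protection. With QLQ-C30 described only before surgery and at 12 months, one missed interview removes a woman from the primary analysis. The two procedures also carry different follow-up, so unequal loss is possible. At stake is a headline estimate that carries the assurance of intention-to-treat while resting on an assumption that is neither stated nor examined.

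**Working it through.** **1. What the rule amounts to.** All randomised patients, minus those with a missing outcome, is the complete-case set. ANCOVA on that set estimates the treatment difference without bias only if missingness is unrelated to the 12-month score given arm and baseline. The condition on baseline helps only if baseline is always in the model.

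**2. The plan's own figure.** The 200 cannot be reproduced because no SD is given, so it can only be solved backwards. Inputs from the article: 200 patients, 90% power, significance level 0.05, allocation 1:2 (LUAL:LAVH), a difference of 10%. Assumptions: 10% means 10 points on a 0–100 scale, and the test is two-sided.

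- Arms: 200/3 = 66.7 and 133.3.
- SE = SD × √(1/66.7 + 1/133.3) = 0.15 × SD.
- 90% power needs 10/SE = 1.960 + 1.282 = 3.242, so SE = 3.08 and SD = 20.57.

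**3. Bias of the complete-case difference.** Let m be the proportion missing in an arm and g the amount by which missing women score worse than observed women, taken as equal in both arms. Each observed arm mean is too favourable by m × g, so

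bias (LUAL − LAVH) = (m_LUAL − m_LAVH) × g.

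Here g is the gap left after baseline adjustment, because ANCOVA removes the part explained by baseline. For the reduced sample, SE = 20.57 × √(1/[66.7(1 − m_LUAL)] + 1/[133.3(1 − m_LAVH)]). The last column is the chance of p < 0.05 when there is no true difference (normal approximation). Every m and g is assumed.

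| Missing LUAL / LAVH | Gap g | Bias, points | SE | Type I error |
|---|---|---|---|---|
| 10% / 10% | 10 | 0 | 3.25 | 0.050 |
| 15% / 5% | 15 | +1.5 | 3.29 | 0.074 |
| 5% / 15% | 15 | −1.5 | 3.23 | 0.075 |
| 20% / 5% | 10 | +1.5 | 3.36 | 0.073 |
| 20% / 5% | 20 | +3.0 | 3.36 | 0.145 |
| 30% / 10% | 20 | +4.0 | 3.55 | 0.203 |

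In the second row the bias is 1.5/3.29 = 0.46 of a standard error and 15% of the assumed 10-point target. The third row swaps the arms, and the sign reverses. In the first row the difference is unbiased, although each arm's mean is overstated by 0.10 × 10 = 1.0 point.

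**4. Power.** If 200 is just enough for 90%, equal loss of a fraction d gives SE = 3.08/√(1 − d). With 10% missing, power is Φ(10/3.25 − 1.96) = 87%. With 20% missing, SE = 3.45 and power is 83%. This is the cost of losing outcomes. It is not a fault of the exclusion rule as such.

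**The case against.** **The rationale is ambiguous.** A reader might infer that the article admits that missing women are those who did badly. The wording is too awkward to carry that, since it can equally mean that the minimum outcome data are lacking. This stands, so informative missingness is one reading and not a stated fact. On the other reading the exclusion is still unjustified and the label still wrong.

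**The direction is unknown.** A reader might infer that the rule flatters LUAL, because women who keep the uterus may have persisting symptoms and drop out. The documents do not support a direction. LUAL patients have 3-monthly uterine and fibroid ultrasound and are asked for monthly bleeding records, whereas the ovarian scans and blood tests in both arms are 6-monthly. Retention could therefore be better on LUAL. This stands.

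**The size is assumed, and complete-case ANCOVA can be valid.** Both are true. If missingness depends only on arm and baseline, the planned analysis is unbiased, and with low or balanced loss the effect is small. The exclusion is also disclosed openly.

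**Power.** A reader might blame the exclusion for lost power. Missing outcomes cost information under almost any method, and imputation recovers little of it without good predictors, so this is not part of the case.

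**Imputation will move little.** With only the outcome missing, imputing from arm and baseline gives essentially the complete-case ANCOVA estimate. The documents do not show that early pain scores, complication grade, haemoglobin or hormones predict 12-month quality of life. This also stands. The main gain is a correct label, a stated assumption and a sensitivity analysis for departures from it.

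**Conclusion.** The concern holds as an inconsistency in the current text: the primary analysis is labelled intention-to-treat on everyone randomised and defined as complete-case. Confidence in that is high. It is also clear that the stated reason does not justify the exclusion.

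Whether the estimate would in fact be biased, in which direction and by how much cannot be settled from the article. Over the assumed inputs the bias runs from zero to 4 points in either direction, with 1.5 points for the 15% versus 5%, 15-point case. These figures rest on assumed missing rates and gaps; the standard errors and type I errors also rest on an SD of 20.57 back-solved under a two-sided test and a 10-point target.

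This should be fixed before the 12-month outcomes are analysed. It does not by itself invalidate the trial.

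**What to change.** 1. Delete the minimum-outcomes rationale.
2. Define the primary set as all randomised patients in their assigned arm. Fit the ANCOVA with baseline QLQ-C30 always included, whatever the test of baseline imbalance shows.
3. Impute missing 12-month scores by multiple imputation within arm under a stated missing-at-random assumption. Use baseline QLQ-C30 and data already collected: postoperative pain VAS, complication grade, 6-month haemoglobin and hormone levels.
4. Report the complete-case ANCOVA under that name, as a sensitivity analysis and not as intention-to-treat.
5. Add a delta-adjusted (tipping-point) analysis that worsens imputed scores separately in each arm until the conclusion changes. Apply the shift in the adverse direction of each scale: a higher rating on a symptom item means more symptoms, so lowering every score would not be uniformly adverse. Shifting LUAL alone could not test losses on LAVH.
6. Report the number missing and the reasons, by arm.

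The cost is revised wording and modest extra analysis, with no new data. The interval may be slightly wider.

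### The primary variable is not identified: the plan names the whole EORTC QLQ-C30, so the 0.05 test and the 90% power belong to no single score

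*Protocol article*

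**What the plan says.** The Abstract and the Primary outcome section under Methods and design name a questionnaire and a time point, but no scale: "Postoperative QOL 12 months after surgical treatment are evaluated using the European Organization for Research and Treatment of Cancer Quality of Life Questionnaire".

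The Primary outcome section under Outcome measurements describes what the questionnaire contains:
- "five functional scales (physical, role, cognitive, emotional, and social");
- "three symptom scales (fatigue, pain, and nausea and vomiting), a global health and QOL scale";
- single symptom items, given as examples: "dyspnea, appetite loss, sleep disturbance, constipation, and diarrhea";
- an item on financial impact.

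Most items have four response levels, and the two global items have seven. No total or summary score is described.

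The Statistical analysis section then refers to the primary variable in three ways:
- The ANCOVA is "to compare the QOL scores on the basis of EORTC QLQ-C30 between the 2 treatment methods" (plural).
- The baseline check opens with "After we consider the overall baseline EORTC score" (one overall score, not defined anywhere).
- The sample size of 200 gives 90% power "to detect a difference of 10% in the EORTC QLQ-C30 score at 12 moths" (singular), labelled the primary outcome, at the 0.05 level.

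No multiplicity rule is stated.

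**The concern.** A primary hypothesis needs one variable, or a defined set with a rule for combining the tests. Here the plural, the overall and the singular score are not shown to be the same thing, and none can be matched to a score in the questionnaire description.

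Two things are at stake. First, a conclusion of difference or of no difference could depend on which scale is reported as primary. Both conclusions matter: the Discussion aims to show similar efficacy, and the article says that a finding of no difference would call for a further comparison with embolization. The planned informal interim look at preliminary results adds the risk that the scale is chosen after data have been seen. Second, the power claim cannot be checked, because it rests on the SD of a score that is not named.

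**Working it through.** **Number of candidate scores.** From the Primary outcome section under Outcome measurements: 5 functional + 3 symptom + 1 global + 5 named single items + 1 financial = 15. The single items are introduced as examples, so 15 is the number listed and may not be the full number.

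**Error rate if every listed score were tested.** Assume 15 tests, each at two-sided 0.05, with no true effect.
- Independent: 1 − 0.95^15 = 0.537, or 54%.
- Equal pairwise correlation (assumed; simulation with 400,000 draws of correlated normal statistics):

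| Assumed correlation | At least one significant |
|---|---|
| 0.3 | about 46% |
| 0.5 | about 36% |
| 0.7 | about 26% |
| 0.8 | about 20% |

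The article gives no correlations, so this is a range.

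**The plan's own figure, N = 200.** It cannot be reproduced, because neither a scale nor an SD is given. It can be solved backwards under assumptions: 10% read as 10 points on a 0–100 scale, two-sided 0.05, 90% power, and the 1:2 allocation from the Study design section (about 66.7 and 133.3 patients).
- SD = 10 / [(1.960 + 1.282) × √(1/66.7 + 1/133.3)] = 10 / (3.242 × 0.15) ≈ 20.6.
- The same calculation at 1:1 gives 21.8. One-sided, it gives 22.8 (1:2) or 24.2 (1:1).

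Reading 10% as a difference between two proportions does not lead to 200. The variants tried (50% v 60%, 80% v 90%, 85% v 95%) need 376 to 1167 patients.

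**Why the choice of scale matters for power.** For 10 points, 1:2, two-sided, with assumed SDs:

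| SD | N for 90% power | Power at N = 200 |
|---|---|---|
| 15 | 108 | 99% |
| 20 | 192 | 92% |
| 25 | 297 | 76% |
| 30 | 426 | 60% |

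Where ANCOVA is used, the SD that counts is the residual SD after baseline adjustment.

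**One variable against fifteen.** A single pre-named variable tested at 0.05 keeps the type I error at 0.05. Testing all 15 with Bonferroni uses 0.05/15 = 0.0033 (critical value about 2.935). At the SD of 20.6, power per scale at N = 200 falls from 90% to Φ(3.242 − 2.935) ≈ 62%, and about 339 patients would be needed for 90%.

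**The case against.** The strongest reply is that the article can be read as having one primary score, incompletely defined. The 0.05 level for the primary outcome appears only in the power sentence, where the score is singular. The baseline sentence is singular too, and the plural in the ANCOVA sentence may simply mean the scores of many patients. On that reading there is one test and no multiplicity.

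This stands to the following extent. A reader might infer that 15 ANCOVAs will each be run at 0.05, and that the trial has no controlled primary test at all. The article does not say so. The error rates above therefore describe a plan that the text permits but does not state. The reply does not rescue the single score, however: if one score is meant, the article does not say which scale it is or how an overall score is formed.

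A second reply is that a condensed article leaves scoring details to the full protocol or the SAP. That covers scoring rules and the order of secondary scales. It does not cover the identity of the primary variable, because the article itself commits to N, power and alpha for it, and describes it in wording that does not agree.

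A reader might also infer that the questionnaire's content has little to do with fibroids. The article does not support that as a general statement: pain and constipation are among the listed scores, and the Background names pelvic pain and constipation as fibroid symptoms.

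**Conclusion.** The concern holds as a failure to identify the primary variable. The whole questionnaire is named, at least 15 scores are listed, no total is described, and the Statistical analysis section moves between three descriptions. The 0.05 test and the 90% power are thus attached to no single variable.

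The error rates of 54%, 46% and 36% are conditional on all 15 scores being tested at 0.05, on no true effect, and, for the last two, on assumed common correlations of 0.3 and 0.5. The implied SD of about 20.6 rests on reading 10% as 10 points and on a two-sided test at 1:2. The article settles neither the meaning of 10% nor the sidedness of the primary test.

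**What to change.** Before any comparative 12-month data are seen, and with the date recorded:

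1. In the Primary outcome and Statistical analysis sections, name one primary variable at 12 months. The global health/QOL scale is the natural candidate, since it is the listed scale named for quality of life. A fully defined summary score would serve equally well.
2. Test it at two-sided 0.05 by ANCOVA with its own baseline value always included as covariate. The undefined overall baseline score is then no longer needed.
3. State whether 10% means 10 points on a 0–100 scale, and give the SD assumed. If the SD for the chosen variable differs from about 20.6, restate the power at N = 200.
4. Make all other scales and items secondary, either with a multiplicity adjustment such as Holm or as estimates with confidence intervals.

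The items are already collected, so the change itself is wording. There are two costs. The other scales can no longer support a primary claim. Recruitment closed in June 2008, so a shortfall in power on the chosen variable can be reported but not made up by enrolling more patients.

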#### Postoperative clinical outcomes

Compared with preoperative status, postoperative clinical outcomes are compared between LUAL and LAVH as follows: anemia, hormonal status and serum CA-125 levels; operation time, hospitalization and recovery time to routine life; postoperative pain; conversion to laparotomy; satisfaction of postoperative sexual intercourse; complications associated with surgery.

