### Secondary outcomes

#### Volume reduction of uterus, uterine fibroids and bilateral ovaries by USG

The method for evaluating volumes of uterus, uterine fibroids and ovaries is as follows: Volume (cm^3^) = maximal sagittal diameter (length, cm) × maximal coronal diameter (width, cm) × maximal antero-posterior diameter (depth, cm) × 0.5233 [13]. Volumes of uterus and uterine fibroids are evaluated in patients treated with LUAL preoperatively and every 3 months, whereas volumes of bilateral ovaries are examined in all patients preoperatively and every 6 months (Fig. 2).

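### Secondary outcomes with a preoperative measurement are assigned unadjusted two-group tests, and the analysed quantity (follow-up value or change) is not fixed; the cost is precision, not bias

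*Protocol article*

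**What the plan says.** In the protocol article, *Statistical analysis*, the baseline-adjusted method belongs to the primary outcome: "Analysis of covariance (ANCOVA) will be applied to compare the QOL scores on the basis of EORTC QLQ-C30 between the 2 treatment methods". For the remaining outcomes the text says "Other comparisons between the 2 groups will be made with the use of a two-sided Student's t-test". Alongside it, continuous outcomes are given the Mann-Whitney U test; categorical ones get a chi-square test. No covariate is named for these.

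Preoperative values exist for six of the continuous secondary outcomes:

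- Acute-phase haemoglobin: "we check serum hemoglobin levels preoperatively and 2 days after surgery for comparing the effect of intraoperative blood loss between LUAL and LAVH". It is measured again every 6 months.
- Serum markers: "serum LH, FSH, E2 and CA-125 levels are checked preoperatively and every 6 months".
- Ovarian volume: "volumes of bilateral ovaries are examined in all patients preoperatively and every 6 months".

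The sections differ on what is compared. The summary of secondary outcomes frames the comparison against baseline: "Compared with preoperative status, postoperative clinical outcomes are compared between LUAL and LAVH as follows: anemia, hormonal status and serum CA-125 levels". It also defines the ovarian outcome as a reduction in volume. The detailed section on clinical outcomes speaks instead of comparing haemoglobin levels and hormone and CA-125 values between the treatments, without mentioning change.

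**The concern.** The article judges these outcomes relative to the preoperative state and collects the measurement needed to do so, but the tests it names have no place for that measurement as a covariate. It already uses the better method for the primary outcome.

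These outcomes matter clinically. Hormones are followed because the article cites a 3.5% rate of elevated FSH after the ligation procedure. Acute haemoglobin is the measure of operative blood loss, and menorrhagia is one of the qualifying symptoms, so preoperative haemoglobin can be expected to vary between women. With 1:2 allocation the LUAL arm is small. An imprecise comparison may end without significance and be taken as reassurance about ovarian function.

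Leaving the analysed quantity open adds to this. A follow-up comparison and a change comparison of the same data have different precision and can give different p-values.

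**Working it through.** **Inputs from the protocol article.** Total 200 patients (*Statistical analysis*) and 1:2 allocation LUAL:LAVH (*Study design*), so 200/3 ≈ 67 on LUAL and 133 on LAVH.

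**The plan's own figure.** The 200 is derived for the QLQ-C30 at 90% power. No standard deviation is stated, so it can only be solved backwards. Reading the 10% difference as 10 points (an assumption), it implies an SD of about 20.6 with a two-sided test and 1:2 allocation. That figure does not bear on this point; the article gives no power figure for the secondary outcomes.

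**Assumptions.** The correlation r between preoperative and follow-up value is not given, so a range of 0.3 to 0.8 is used. Variance is taken as equal at both times and in both arms.

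**Formulas.** Variance of the treatment difference, relative to a test on the follow-up value alone:

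- follow-up value only: 1
- change from baseline: 2(1 − r)
- ANCOVA: 1 − r²

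ANCOVA relative to the change score is (1 − r²) / [2(1 − r)] = (1 + r)/2.

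| r | Change, 2(1 − r) | ANCOVA, 1 − r² | ANCOVA saving vs follow-up only | ANCOVA vs change, (1 + r)/2 | ANCOVA saving vs change |
|---|---|---|---|---|---|
| 0.3 | 1.40 | 0.91 | 9% | 0.65 | 35% |
| 0.5 | 1.00 | 0.75 | 25% | 0.75 | 25% |
| 0.7 | 0.60 | 0.51 | 49% | 0.85 | 15% |
| 0.8 | 0.40 | 0.36 | 64% | 0.90 | 10% |

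**In terms of power.** The standard error of a follow-up-only difference, in SD units, is √(1/66.7 + 1/133.3) = 0.15. A difference of (1.96 + 0.84) × 0.15 = 0.42 SD then has 80% power at two-sided 5%. For the same difference:

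| r | Follow-up only | Change score | ANCOVA |
|---|---|---|---|
| 0.3 | 80% | 65.8% | 83.6% |
| 0.5 | 80% | 80.0% | 89.9% |
| 0.7 | 80% | 95.1% | 97.5% |
| 0.8 | 80% | 99.3% | 99.7% |

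Which unadjusted analysis is better depends on r: the change score loses to the follow-up value below r = 0.5 and beats it above. ANCOVA has the lowest variance of the three at every r in the table.

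**The case against.** The strongest reply is that the article names tests, not the variable they are applied to. A reader might infer that the preoperative values are thrown away. The documents do not establish that. The summary of secondary outcomes refers to preoperative status, the ovarian outcome is a reduction, and pairing preoperative with day-2 haemoglobin suggests a drop. A t-test on change fits all three and uses the baseline. This stands: against that reading the loss is the smaller one at high correlation, 15% at r = 0.7 rather than 49%. It does not remove the point, because the change score is still less efficient than ANCOVA and the wording about levels and values keeps the other reading open.

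A reader might also infer that unadjusted comparisons mainly reflect how the women differed before surgery. That would be confounding. Allocation is randomized, central and concealed, so unadjusted tests are unbiased in expectation and hold their error rate.

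A third inference is that both tests will be run on every outcome and the better p-value reported. Naming the two together is common shorthand for choosing one by distribution, and the rule for choosing may stand in an analysis plan not shown. Even on the worst reading the excess is modest: in 20,000 simulated null trials at 67 versus 133, counting either test at p < 0.05 gave a type I error of 6.2% for normal data and 7.5% for lognormal data (log-SD 1).

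Finally, these are secondary outcomes and the correlations are assumed. Both are true. Nothing suggests that haemoglobin, four serum markers and ovarian volume share one correlation, so the gain will differ between them.

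**Conclusion.** The point holds as a matter of precision and clarity. The article states an unadjusted method for continuous secondary outcomes whose baselines it collects, and does not fix whether follow-up or change is analysed. ANCOVA improves on either reading: by 9% to 64% of variance against follow-up only, and by 35% to 10% against change, as r goes from 0.3 to 0.8. These figures rest on the assumed range of r and on equal variances; the documents supply neither.

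The documents do not support calling the planned tests biased or invalid, saying that baselines are discarded, or saying that two tests will be reported per outcome. The primary comparison is unaffected. The change is worth making because the affected outcomes include the ovarian and anaemia comparisons, the LUAL arm has about 67 women, and the cost is close to nil.

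**What to change.** In *Statistical analysis*, replace the unadjusted test for each continuous between-arm secondary outcome with a preoperative value (haemoglobin, LH, FSH, E2, CA-125, ovarian volume) by ANCOVA at each follow-up time:

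- response: the follow-up value; covariates: arm and the preoperative value of the same measure, included in every case;
- log scale for response and covariate where the marker is skewed, as may be expected for the hormones and CA-125;
- report the adjusted difference, or the ratio of geometric means on the log scale, with a 95% confidence interval.

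Keep an unadjusted test, one named per outcome, only where there is no baseline: operation time, hospital stay, recovery time and the summed pain score. Bring the sections on clinical outcomes into line so that they name the same analysed quantity.

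The cost is analysis wording only. No new data, visits or patients are needed, and the method is already in use for the primary outcome.
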